### The PAC intervention: similarities and differences between CBT and PEP versions

Both intervention arms in the trial are the same in frequency of contact (16 sessions), content (identical information is delivered), mode (group format), duration (60 – 90 minutes per session), intervention goals (related to nutrition and physical activity), and the number of group leaders (two per group). Importantly, the intervention arms differ in how information is conveyed to parents, and how parents work towards attempting, achieving, and maintaining healthy cognitive and behavioural changes. All families are encouraged to manually monitor their daily nutrition, moderate-to-vigorous-physical activity (MVPA), sleep and leisure-time screen time (LTST) throughout the intervention period, and tracking tools are available for all family members (parents, children, other family members). To encourage monitoring, small prizes (e.g., cookbooks, activity-promoting toys and games) are awarded at three points during the 16-session intervention period (e.g., on week 6 for tracking completed in weeks 1 – 5, on week 11 for tracking completed in weeks 6 – 10, and on week 16 for tracking completed in weeks 11 – 15). Families are eligible to receive prizes in each of the three time periods regardless of their consistency with monitoring in previous time frames. For both CBT and PEP, families strive to achieve the same lifestyle goals (please see Table 2), which are based on evidence-based recommendations [55-57].

**Table 2 T2:** Lifestyle goals for the CBT and PEP Versions of the PAC intervention

	
**1. Diet**	Daily vegetable and fruit intake: ≥5 servings
	Daily grain product intake: ≥50% servings as whole grains
	Daily sugar-sweetened beverage intake: 0 servings
**2. Physical Activity**	Daily steps: ≥12,000 (girls); ≥15,000 (boys)
	Daily moderate-to-vigorous physical activity: ≥90 minutes
**3. Sedentary Activity**	Daily leisure time screen time: ≤90 minutes

Fundamental differences do exist between the CBT and PEP interventions. CBT is a theoretically-based therapy that focuses on the role that cognitive processes play in the maintenance of problem behaviours, mood states, and habits [58]. CBT also highlights the relationship between thoughts, feelings and actions, and utilizes techniques involving motivation, goal-setting, problem-solving, and knowledge/skill acquisition that can facilitate sustainable behaviour changes [59]. This intervention is designed to promote parental adoption of a more authoritative parenting style, which is exemplified by elements including rational decision-making, verbal give-and-take, autonomous self-will, and disciplined conformity. CBT can improve parenting style and parent–child interactions [60], so group leaders work with parents who have more permissive (e.g., makes few demands) or authoritarian (e.g., restricts child autonomy) parenting approaches to help them to develop authoritative parenting skills. The skills learned in CBT help parents to identify and change the parenting mechanisms that maintain their children’s current lifestyle habits; group leaders help parents to link knowledge, attitudes, thoughts, and feelings to behaviours and facilitate setting incremental goals that build on one another week-to-week in a manner that corresponds to parent motivation. CBT encourages consistent participation and collaboration between group leaders and participants; a Socratic questioning approach is also applied to help parents find their own answers to problems instead of having questions answered or problem-solved by group leaders [61]. To ensure the CBT-based version adhered to the main tenets of cognitive behavioural interventions, we consulted an international, three-member panel of clinical and research experts in CBT, obesity, and intervention development and evaluation. Their critical evaluation, feedback, and recommendations for revisions were incorporated into the curriculum.

In contrast, PEP is a knowledge-based intervention that is modeled after traditional nutrition and health education programs. Information regarding healthier parenting styles is provided in a didactic manner without directive leader-initiated goal-setting or problem-solving. In relation to CBT, PEP is a more passive intervention and there is limited focus on active skill building. The intervention is predicated on a more traditional approach that assumes behaviour change results from increased knowledge, although different activities are included for parents that encourage learning (individual activities, brain-storming, hands-on experiential learning) [62]. While group discussions and problem-solving are included within PEP, active integration of learned concepts in goal-setting and linking cognitions and behaviours to lifestyle changes are not integral. There is no active cognitive or behavioural skill building process embedded in the program. In relation to CBT, PEP requires less investment of energy and participation from parents, which many parents prefer. While PEP does not represent a true control group, its content and delivery are consistent with what many clinicians provide for weight management.

### Intervention fidelity

One of the challenges in evaluating the effectiveness of lifestyle and behavioural interventions is optimizing the fidelity with which the interventions are delivered. In other words: During the trial, are the interventions delivered in the way in which they are intended? We are using multiple strategies to ensure standardization and consistency across parent/child cohorts as well as within and between intervention arms. Group leaders receive intervention delivery training through the use of standardized intervention manuals and weekly clinical meetings; following a manual and receiving reinforcement through team meetings ensures the interventions are delivered in a standard and consistent manner. Manualization of interventions is used extensively in health fields [63-66] and adds methodological rigor to our study design. Evaluation of delivery (adherence to intervention manuals) is achieved by session videotape. Three sessions within each of the CBT and PEP intervention arms are randomly chosen for videotaping and subsequently scored for adherence by two independent evaluators using a template created for the study that highlights study content and unique features of the interventions (See Table 3 for intervention adherence checklist). Inter-rater reliability is calculated using the Kappa statistic [67]. Issues with non-adherence to intervention integrity are addressed during weekly meetings.

**Table 3 T3:** Intervention integrity checklist for the PAC intervention

Group Leader #1: __________________________________			Date (dd/mm/yyyy): ________________	
Group Leader #2: __________________________________			Rater: ___________________________	
**Content** – Are the following content items addressed in the session?			**Yes**	**No**
(Note: Details to be included by investigators; content items vary session-to-session)				
__________________________________________________________________________________________________________________				
__________________________________________________________________________________________________________________				
__________________________________________________________________________________________________________________				
__________________________________________________________________________________________________________________				
__________________________________________________________________________________________________________________				
**Content** – Did leaders follow the manual content throughout the session?				
(Rater: Please read along in the manual during session to evaluate adherence to content).				
Additional comments:				
___________________________________________________________________________________				
___________________________________________________________________________________				
___________________________________________________________________________________				
___________________________________________________________________________________				
___________________________________________________________________________________				
		
**Group Process Foundations**	**Leader 1**		**Leader 2**	
	**Yes**	**No**	**Yes**	**No**
Leader linked parent experiences to individual factors (e.g., linked the impact of parent, child preferences on experiences).				
Leader linked parent experiences to family factors (e.g., linked the impact of family members on parent experiences).				
Leader linked parent experiences to environmental factors (e.g., linked the role of community and available resources on parent experiences).				
Leader made links between thoughts, feelings and behaviours.				
Leader reflected questions back to group.				
Leader answered questions directly.				
Leader shared personal anecdotes/stories in response to parents sharing their experiences.				

### Outcome measures

Child BMI z-score is the primary outcome for this study. Several investigations [68-72] have included BMI z-score as the primary outcome in pediatric weight management studies since it represents a clinically-meaningful indicator of weight status in childhood. Beneficial changes in this variable are linked to improvements in obesity-related risk factors for chronic diseases including insulin resistance, dyslipidemia and high blood pressure [73,74]. The inclusion of this outcome is also informative when comparing effect sizes across studies.

Consistent with recommendations for evaluating the effects of pediatric obesity treatment [12,17], we are measuring a number of secondary physiological, behavioural, and psychosocial variables in families. Along with assessing nutrition and physical activity behaviours, anthropometry, and cardiometabolic risk factors, we are testing potential moderating (e.g., sex, age) and mediating (e.g., parents’ lifestyle behaviors) variables to explore how different child and parent features interact with and respond to the different interventions and hypothesize how they contribute to changes in child health outcomes [75]. This is a valuable, but often overlooked process that provides a better understanding of the mechanisms of lifestyle change. This approach, in turn, allows our team to improve our interventions since we can distinguish between effective and ineffective intervention components [76].

#### Physical exam, medical history, and demography

Physical exams (for children) and a family medical history interview (for parents) are conducted by a pediatric endocrinologist at clinic intake. In addition, children’s physical development are determined according to established guidelines [77,78]. Demographic data (e.g., date of birth, ethnicity, parents’ education, household income) are also collected.

#### Anthropometry

Anthropometric measurements for children and parents are collected using a standardized protocol. Height is measured (without shoes) to the nearest 0.1 cm using a Seca 242 wall-mounted electronic stadiometer (Seca, Hamburg, Germany). Weight is assessed (wearing light clothing) to the nearest 0.1 kg using a Seca 644 medical scale. BMI is then calculated. For children, BMI data are entered into *EpiInfo* (Center of Disease Control and Prevention, Atlanta, GA) to determine sex- and age-specific BMI z-scores and percentiles. Waist circumference (WC) is measured at the top of the iliac crest using a spring-loaded Gulick anthropometric tape (FitSystems Inc., Calgary, AB). WC data are acquired using the following protocol: Measurements are performed with the tape measure snugly positioned on, but not compressing, the skin; the spring is pulled until calibration tension is achieved on the tape. Clothing is positioned so the abdomen is exposed (bottom of shirt is positioned below the arms, which are crossed over the chest; pants/shorts are loosened and lowered slightly to reveal the hips). Recordings are taken at the end of a normal expiration and not during breath holding or abdominal muscle contractions. This procedure is repeated, and if the first and second values differ by more than 0.5 cm, a third measurement is taken. Values are then averaged and recorded to the nearest 0.1 cm.

#### Dietary intake

Dietary intake is recorded prospectively by children and parents over four consecutive days, and includes one weekend day. Once records are returned by families, a registered dietitian (RD) reviews all nutrition information with families to clarify items, validate portion sizes and name brands, and to ensure data completeness. Subsequently, these data are entered into the *Food Processor Diet Analysis* software program (ESHA Research, Salem, OR) to determine number of servings from *Eating Well with Canada’s Food Guide *[55], total energy, macro-nutrient, and dietary fiber intakes.

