### Timeframe

Data are collected from families at pre-intervention, post-intervention, 6-, and 12-months follow-up. For practical reasons, at each time point, data collection occurs within a 2-month window (e.g., within 8 weeks before the first PAC session, within 8 weeks after the last PAC session, and between 4 weeks before to 4 weeks after each of the 6- and 12-month follow-up time points). Clinical and research experience by our team [48] revealed that this timeframe is needed to accommodate families’ schedules and clinical capacity to complete data collection, which also differentiates our real-world, comparative effectiveness research [51] from more stringent criteria that are applied in the context of efficacy studies. Data collection is completed by clinicians working within the PCWH, and given the real-world, applied health services environment within which the study is conducted, we are unable to blind them from knowing which families are receiving the CBT- and PEP-based versions of the PAC intervention [52].

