### The PAC interventions: design and delivery

The PAC curriculum (please see Table 1) was developed using strategies consistent with intervention mapping [53] by incorporating evidence-based, lifestyle and behavioural strategies for pediatric weight management [54]. Both the CBT and PEP interventions consist of 16 weekly sessions that are offered to parents (in the evening) twice yearly (September – December; January – April). Sessions are held within our health care institution in classrooms within different areas of the hospital as a means to minimize cross-group contamination. Two healthcare professionals (e.g., dietitian, nurse, fitness professional, mental health professional) per intervention arm provide the curriculum to small groups of parents that will range in size to no more than 15 parents/group. Although at least one parent per family is required to attend the group sessions, additional parents or caregivers are welcome.

**Table 1 T1:** An overview of the Parents as Agents of Change (PAC) intervention curriculum

**Session**	**Title**	**Content overview**
1	*Welcome*	Introduction and orientation; parents receive pre-intervention snapshot of their children’s lifestyle, behavioural and metabolic health measurements, which is used throughout the intervention to inform decisions regarding behaviour change priorities and goal-setting
2	*Food For Thought*	Canada’s Food Guide, PAC nutrition goal #1 (intake of vegetables and fruit)
3	*More Food For Thought*	Canada’s Food Guide, PAC nutrition goals #2 (intake of whole grain products) and #3 (intake of sugar-sweetened beverages)
4	*It’s Your Move*	Canada’s Physical Activity Guide for Children, PAC physical activity goal #1 (steps / day)
5	*Screensavers*	Canada’s Physical Activity Guide for Children, PAC physical activity goal #2 (leisure time screen time)
6	*Portion Distortion*	Food labels, serving sizes *vs* portion sizes
7	*Move It!*	Canada’s Physical Activity Guide for Children, PAC physical activity goal #3 (moderate-to-vigorous physical activity)
8	*Staying On Track*	Behaviour change relapse prevention
9	*Get A Cue!*	Social cues influencing nutrition and physical activity
10	*Positive Parenting Partnerships*	Limit-setting, boundaries, communication
11	*Community Connections*	Environmental factors influencing nutrition, physical activity
12	*Eating Out, Eating Healthy*	Menu reading, providing healthy lunches
13	*Feelin’ Groovy!*	Healthy self-esteem and body image

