#### Physical activity and sedentary behaviours

Children and parents measure prospectively their total physical activity using a pedometer (Yamax Digi-Walker SW-200) over a 7-day interval that overlaps with their dietary intake recording. Families receive training on proper pedometer positioning, data recording, and other physical activity monitoring details before the measurement interval starts. To ensure proper functioning, all pedometers are calibrated prior to use by way of a standardized step count test. Since pedometers do not capture information regarding physical activity intensity, children and parents complete simultaneously a 7-day physical activity record to document quality, quantity, and patterns of moderate-to-vigorous physical activity, leisure-time screen time (television, computer, video game, etc.), and sleep duration. Once records are returned, data are reviewed with families to ensure completeness and clarify durations and intensities of activities.

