It is also important to acknowledge the potential limitations of this study. First, while we are implementing several retention strategies (e.g., regular telephone calls to confirm appointment and session attendance, modest incentives for families to complete outcome assessments at study time points), we know from our own clinical and research experience [48] and the published literature [94] that lack of engagement and attrition are common phenomena in pediatric weight management. These issues may have a negative impact on family recruitment and retainment within this RCT. To better understand and potentially address issues of engagement and attrition, we are currently completing an independent multi-center, qualitative study to interview 100 parents and 100 children and youth with obesity in order to understand parents’ and children’s decisions regarding engagement in and attrition from pediatric weight management centers [95]. These emerging data should help to inform decisions that should optimize recruitment and retention in the current study. Second, there is an increasing number and variety of services that relate to pediatric weight management (i.e., physical activity and exercise programs for families, community-based weight management programs, and outpatient nutrition) available to families in the Edmonton-area. Although this is advantageous from family and health services viewpoints, this reality decreases the number of local families who may be enrolled in our study. Third, our study is conducted in an outpatient clinic setting, so the health professionals performing many of the outcome assessments (e.g., anthropometry) know which families were randomized to the CBT and PEP intervention groups. Although they have no vested interest in the study as study co-investigators, this real-world environment introduces a potential source of bias (lack of assessor blinding; [52]) because all families receiving weight management care are regularly discussed during weekly case conference team meetings. Finally, to date, our discussions with families regarding a PAC approach for managing pediatric obesity have occasionally been met with resistance; since children present with the identified health concern, parents are sometimes taken by surprise with the primary role they are asked to play in the PAC intervention. Many parents embrace their leadership role in making and sustaining healthy changes within their families, although other parents will prefer that intervention efforts focus on children themselves or include both parents and children. As a consequence of these differing perspectives and intervention foci, some parents decline study participation.

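### Clinicians who know the arm review self-reported diet and activity records with families at follow-up, and the disclosed lack of assessor blinding comes with no safeguard for this judgement-based step

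*Protocol article*

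**What the plan says.** All references are to the protocol article.

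- **Timeframe.** "Data collection is completed by clinicians working within the PCWH", and of these clinicians it says "we are unable to blind them from knowing which families are receiving the CBT- and PEP-based versions of the PAC intervention".
- **Dietary intake.** Children and parents keep a four-day food record. Once it is returned, a registered dietitian "reviews all nutrition information with families to clarify items, validate portion sizes and name brands, and to ensure data completeness". The next step begins "Subsequently, these data are entered into the" diet analysis software, which produces food-guide servings, energy, macronutrients and fibre.
- **Physical activity and sedentary behaviours.** A seven-day record covers moderate-to-vigorous activity (MVPA), screen time and sleep. After its return, "data are reviewed with families to ensure completeness and clarify durations and intensities of activities". The reviewer's role is not named here.
- **Randomization.** Assignment comes after the pre-intervention assessments.
- **Statistical analysis and Outcome measures.** Outcomes are analysed as percent change from pre-intervention to each later time. Secondary outcomes follow a process similar to the one-sided t-test for the primary. Meeting food-guide recommendations is compared with a one-sided test of proportions. Parents' lifestyle behaviours are given as an example of a mediator.
- **Strengths and limitations.** Lack of assessor blinding is admitted as a potential source of bias, with anthropometry as the example. The accompanying reassurance is "Although they have no vested interest in the study as study co-investigators". Families are discussed at weekly team conferences.

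**The concern.** Height and weight are read from instruments under a standard procedure. A conversation about how large a portion was, or whether an activity was moderate or vigorous, leaves much more room for judgement. A reviewer who knows the arm may probe differently without intending to, and a family may answer differently depending on what it thinks the reviewer hopes to hear. The values that leave this conversation are the outcome data.

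The outcomes at stake are the ones meant to show whether CBT changed behaviour: diet, recorded MVPA, screen time, sleep and the food-guide categorical outcome. The mediation analyses that use parents' lifestyle behaviours rest on the same records. A reporting difference created at review could be read as a behavioural effect or as a mechanism, or could mask a real one.

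**Working it through.** The plan states no figure on this point, so the check sets its sections side by side. A short illustration follows.

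**Text check**

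1. *Is the reviewer aware of the arm?* Timeframe assigns data collection to clinic clinicians and says they cannot be blinded. The dietitian's review is part of data collection. The activity review names no role, so it falls under the same statement.
2. *Can the review change the data?* The article speaks of clarifying and validating, not of revising. But the review comes before software entry, and checking portion sizes or activity intensities has a purpose only if entries may change. That entries change is therefore an inference, though a close one.
3. *Does baseline cancel the effect?* No. Assignment follows the pre-intervention assessments, so no arm exists when the baseline records are reviewed (taking that review as part of those assessments). At post-intervention, 6 and 12 months the arm is known. A differential shift at follow-up passes into the change score with nothing at baseline to offset it.
4. *Do the stated protections reach this step?* The blinded biostatistician receives the data after the review. Parents do not know how the two modalities differ, but that does not stop a reviewer who knows the arm from prompting differently. The comment about co-investigators concerns vested interest, not knowledge of the arm.
5. *Which outcomes are exposed?* Those taken from the reviewed records, all secondary. BMI z-score comes from measured height and weight. Pedometer steps are a device count and are less exposed.

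**Illustration (the shifts are assumed; the article gives no error data)**

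Inputs: 30 families per arm with post-intervention data (Sample size); a one-sided 0.05 t-test (Statistical analysis, reading the similar process for secondary outcomes as one-sided too); no true difference; a shift of d standard deviations of the analysed change, towards CBT, caused only by the review.

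Normal approximation: rejection rate = Φ(d × √(n/2) − 1.645), with √(30/2) = 3.873. The last column is the exact t-test calculation.

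| d (assumed) | d × 3.873 − 1.645 | Φ | t-test |
|---|---|---|---|
| 0 | −1.645 | 5% | 5% |
| 0.1 | −1.258 | 10% | 10% |
| 0.2 | −0.870 | 19% | 19% |
| 0.3 | −0.483 | 31% | 31% |
| 0.5 | 0.291 | 61% | 61% |

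A shift the other way would hide a true benefit. At d = −0.2 the same formula gives Φ(−2.420), about 1%. The table shows how sensitive the test is to a shift. It does not estimate what will happen in this trial.

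**The case against.** The strongest reply is that the article has already disclosed the matter. It says the clinicians cannot be blinded, gives the practical reason, and names lack of assessor blinding as a potential bias. Anthropometry is only an example there, so diet and activity records are not excluded, and the remark about vested interest is a concession within that admission. This stands: the limitation is neither hidden nor dismissed. What remains is that disclosure does not reduce bias, and the step with the most judgement has no described protection.

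A second reply is that prompt lists and record-keeping rules belong in a full protocol or manual. That is also fair, and such rules may exist. But the review by staff who know the arm is stated outright, so the point does not rest on their absence alone.

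A reader might go further in three ways that the documents do not support:

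- *That a family's own group leader reviews its records.* The article says "Two healthcare professionals (e.g., dietitian, nurse, fitness professional, mental health professional) per intervention arm provide the curriculum" and does not separate the roles, but it nowhere says that leaders review their own families. In a condensed article that silence proves nothing.
- *That MVPA and screen time are scored against the goals in Table 2.* Those are goals for families. The analysis uses percent change, and the only categorical outcome named is meeting food-guide recommendations.
- *That the bias favours CBT.* CBT is the more goal-directed arm, so asymmetry is plausible. Yet both arms share the same goals, self-monitoring and prizes, and a wish to report success could act in either.

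**Conclusion.** The point holds for secondary outcomes. At post-intervention and follow-up, self-reported diet and activity records are reviewed with families by staff who know the arm, whereas the baseline review is made before any arm exists. The resulting comparisons of diet, MVPA, screen time and sleep, the food-guide outcome, and mediation analyses using parents' lifestyle behaviours could be shifted differently by arm. The primary BMI z-score is untouched by this route.

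Size and direction cannot be derived from the article. The conclusion assumes that the review can alter entries, that the activity reviewer is one of the clinicians described under Timeframe, and that no fuller document already standardises the review. If one does, citing it would settle much of the point. This is an inexpensive improvement worth making, not a flaw that threatens the main result.

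**What to change.** The changes work within the stated constraint that clinicians cannot be blinded:

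1. Use one fixed prompt list for the diet review and one for the activity review, identical for every family and time point.
2. Keep the family's original entry beside any change, and log each change.
3. Do the diet software entry and the MVPA and screen-time coding from records that carry a study ID only, without arm. This protects most when the coder is not the person who held the review.
4. Compare the frequency and direction of changes between arms. Repeat the main child diet and activity comparisons on original entries, where these are complete enough, as a sensitivity analysis.
5. Where existing staffing allows, have a family's records reviewed by someone other than its own group leader. Alone this would not be enough, because the weekly conferences make the arm known to the whole team.
6. Extend the stated limitation on assessor blinding to name the record review.

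Cost: some extra logging and a second data entry for the sensitivity analysis. Unreviewed records are noisier, so that analysis supports the main one and does not replace it; it also leaves families' own reporting bias in place. Item 5 makes scheduling slightly less flexible. The number of dietitians is not given, so it should stay conditional. Items 1 to 4 need no new staff.
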